### 5.6.5. Risks associated with blood draws, intravenous catheter insertion, non-invasive tests

Chest radiograph

*Likely:* The volunteer will be exposed to a small amount of radiation (0.01 rem), which is 0.2% of the allowable annual dose for radiation workers.

*The risk from radiation exposure of this size is too small to be measured directly. Participants will be provided with a “Radiation Fact Sheet” supplied by the Washington University School of Medicine, Division of Nuclear Medicine.

Blood draws and i.v. catheter insertion:

*Less Likely:* The insertion of a needle into a vein sometimes causes discomfort, bruising, or bleeding at the site of needle insertion. Occasionally some people experience dizziness or feel faint when a needle is placed in their arm.

*Rare:*The insertion of a needle into a vein rarely causes inflammation or infection.

Spirometry:

*Less Likely*: The effort required for a good spirometry test may cause shortness of breath. However, participants will be allowed to take rest breaks between measures if needed. Occasionally, during spirometry, people have experienced dizziness, wheezing, chest pain, racing or pounding heart, an upset stomach, severe shortness of breath, or coughing.

*Rare:*Rarely, people have fainted during spirometry. The test will not be continued in such a case.

Pregnancy:

The medications used for the bronchoscopy and the radiation exposure can cause birth defects and mental retardation to a fetus. All women volunteers for this study will have had a negative pregnancy test prior to further participation.

### 5.6.6. Risks associated with coded data

*Rare:* Each participant enrolled will have a consecutive patient ID number under which data will be coded. In addition, the following information may be used in association with coded data: initials and date of birth. There is a remote possibility of a breach of confidentiality. De-identified data will be stored indefinitely. Identifiable data will be destroyed 5 years after completion of the protocol.

## Adequacy of Protection Against Risks

- - 1. **Recruitment and Consent**

We will not enroll volunteers who work within our department. We will not schedule admission to the CRU until the volunteer has had a chance to read the entire consent and allowed as much time as they require to consider participating (there is no time pressure in which the volunteer must make their decision). We have added additional reminders regarding human research participants’ rights at the beginning of the informed consent.

Since this is an elective study, all participants will be given a written copy of the consent to read and discuss with the investigator or study coordinator more than 24 hours prior to making a decision about their participation. Volunteers will be allowed all the time they want to think about, and discuss, their decision to participate.

Initial discussion of the study with the trained research coordinator working with the principal investigator will occur at the WUSM Volunteer for Health office, the Center for Clinical Studies, or over the telephone. The investigator, co-investigator, or a research fellow (trained in the protection of human subjects for this study protocol) will review the consent with participants in the CRU at the time of their admission. All personnel have received instruction on the Responsible Conduct of Research.

- - 1. **Protections Against Risk**

We have chosen sequential enrollment into the study drug treatment groups so that we can effectively monitor for serious adverse events possibly associated with each drug treatment.

All reasonable measures will be taken to protect the confidentiality of clinical records and research data. The identity of the participants will not be revealed in any publication that might result from this research. Individuals involved in conducting this research project will have access to material collected from these research participants. The confidentiality of all study related records will be maintained according with State and Federal laws.

Results of interventions and evaluations of participating volunteers will be recorded in a clinical source document. These records will be stored in files locked within the investigator’s office and on local WUSM office computers with restricted access, and in the CRU medical records room, which also has access restricted to trained health care professionals.

Initial inclusion/exclusion criteria, physical exam, chest x-ray, ECG, spirometry, and blood tests are to assure us that we only enroll healthy volunteers with intact pulmonary function.

All necessary and appropriate procedures will be taken to prevent and monitor for the early detection of bronchoscopy-related complications. Continuous intravenous vascular access, supplemental oxygen, ECG, and pulse oximetry monitoring will be maintained during the bronchoscopy and for a minimum of 2 hours post bronchoscopy. BAL will be limited to one lobar segment or subsegment, and limited to three 50 ml instillations. Biopsies will not be performed.

Endotoxin has been given many times to healthy research volunteers by injection into a vein, or by inhalation of a mist of endotoxin. Recently, an NIH-sponsored study showed that instillation of endotoxin into a single small section of the lung resulted in an area of lung inflammation that can be triggered with doses 10-30 times smaller than those typically used when endotoxin has been inhaled as a mist.[35](#_ENREF_35) Another advantage of bronchial instillation of endotoxin is that rather than challenging the whole lung with endotoxin, the majority of the lung tissue is not affected by the endotoxin. Nick et al, investigators from another institution other than the NIH, recently reported a study with this same protocol without serious or unexpected adverse events.[39](#_ENREF_39) We also have reported 2 studies including 36 subjects in total without any serious adverse events.

In order to minimize lower airway bacterial contamination during bronchoscopy, volunteers will receive one tablet of oral sulfamethoxazole/trimethoprim (80/400) or one tablet of oral amoxicillin (500 mg.) 12 hours before the bronchoscopy is scheduled, and again immediately before the procedure. Participants will be NPO beginning at midnight to reduce the risk of aspiration during the bronchoscopy.

Extensive procedures have been set up and approved by our IRB and the FDA for monitoring of the participants during and after all procedures. Specific criteria have been established for discharge from the CRU and for follow-up after discharge. These criteria include specific definitions of adverse and serious adverse events, as described above.

Volunteers and their research specimens will be de-identified for the purpose of data collection into case report forms for analysis, using a letter designating the study and a numbering system to designate enrollment number. PET studies are coded sequentially in the order in which they have been completed. Individuals will have an ID number, as well as a separate PET study number for each PET study completed. Data and clinical records will be stored securely, locked in the investigator’s office or the medical records room at the CRU. Deidentified data, including photographs obtained of the airways during bronchoscopy, will be stored indefinitely, but all identifying source documents will be destroyed 5 years after the research is completed.

All efforts will be made to reduce the dose of radiation that research volunteers are exposed to, including ongoing review of data to determine the minimum dose of radioactive tracer and minimum requirements for an adequate CT scan. To minimize risk associated with radiation exposure, pregnant and lactating women and children 18 years old or younger are excluded from participation. In order to reduce radiation exposure, participants will be instructed to empty their bladders immediately after PET scanning is completed (about 70 minutes after tracer administration).

1. **DATA ANALYSIS/STATISTICAL METHODS**
   1. **Sample Size Calculation**

Our recently completed drug treatment study in healthy volunteers receiving intrabronchial endotoxin demonstrated an approximately 50% decrease with ~25% standard deviation in the *K*i after treatment with lovastatin when compared to placebo (see Preliminary Data Section). A sample size of N=6 in each group will allow us to detect a similar magnitude of difference with approximately the same amount of variability in the measurement (23% standard deviation of residuals) with a power of 0.8 and alpha of 0.05.

- 1. **Statistical Analysis**

An interim analysis will be performed after the first treatment group is filled. If there is a minimum of a 30% drop in the post-endotoxin *K*i from the baseline *K*i, enrollment will continue into the next 3 groups. If no change in *K*i is observed at this interim analysis, we will continue to enroll volunteers into the zileuton+placebo and placebo+placebo groups but will not enroll volunteers into the pioglitazone+zileuton group. We recognize that this approach reduces the power of the study but felt this was justified as we would still be able to adequately test our hypotheses while minimizing the risks to the volunteers for this study. At the end of the study, a three-way mixed model analysis of variance (zileuton, pioglitazone, and time ANOVA) will be used to assess the effect of the drug treatments on change in *K*i from baseline and *K*i, after treatment, the primary endpoints among the treatment groups. Appropriate prespecified contrasts will be used for the primary tests. An exploratory analysis using a two-way ANOVA will also be performed to analyze the treatment effects on the BAL total cell counts, BAL neutrophil counts, PPAR-γ transcriptional activity, LXA4, LTB4, IL-8, and TNF-α levels (by ELISA) in the BAL fluid, and 5-LO, 15-LO and PPAR-gamma mRNA levels in BAL cells, although this study will not be powered specifically to detect these relationships. Correlations between the post-endotoxin *K*i and the BAL and urine variables will be performed using standard linear regression with calculation of the coefficient of determination (R2). Correlations will also be explored among serum and BAL measurements and *K*i. The BAL results obtained from healthy volunteers without endotoxin exposure will also be included in this analysis. Any volunteer with incomplete scan data will not be included in the analysis. Any other missing data (i.e. missing BAL data point) will be handled by excluding that data point from that particular analysis. We will also assure that no bias was introduced by this handling of the missing data by using multiple imputation for all missing data.

Correlations will also be explored between serum measurements and both *K*i and BAL measurements. CT density and airway thickness will also be correlated with *K*i and BAL measurements. Respiratory-gated SUV will be correlated with SUV from non-gated PET data as an exploratory analysis to determine the potential value of respiratory-gating for this imaging application. The presence of TLR4 polymorphisms will be correlated with *K*i and BAL measurements to explore whether these SNPs predict hypo-responsiveness to endotoxin as previously published[28](#_ENREF_28).

1. **STUDY ADMINISTRATION**

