**Trial Design**

This is a single center, prospective, single-blind placebo-controlled clinical trial. Twenty-four healthy volunteers will be recruited sequentially into the following four treatment groups in this order: pioglitazone plus oral placebo, zileuton plus oral placebo, pioglitazone plus zileuton, or two oral placebos. All volunteers will be blinded to the study drugs. They will then receive endotoxin instilled bronchoscopically in the right middle lobe. Enrolled volunteers will receive their assigned drug treatment as an outpatient and then undergo a baseline FDG-PET scan on Admission Day 1, receive endotoxin on Admission Day 2, and undergo a post-endotoxin FDG-PET scan followed by bronchoalveolar lavage (BAL) on Admission Day 3. Deidentified tissues from healthy volunteers who donated them for future research use will also be obtained for comparison.

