Several years ago,[35](#_ENREF_35) investigators at the NIHshowed that focal, limited, airway and surrounding parenchymal inflammation could be safely induced by the direct bronchial instillation (intrabronchial, i.b.) of small amounts of endotoxin into the airway of a single lung segment in 20 healthy non-smoking human research volunteers. Neutrophil concentrations in the BAL from challenged lung segments increased by 32-fold 24 h after endotoxin instillation but were back to near control values by 48 h. Since the publication, the model has been employed in an additional 154 subjects, described in 7 additional publications, including two by our own group. To date, there have been no unexpected adverse events associated with use of this model. The potential clinical relevance of this model is supported by a study showing that proteomic patterns in BAL recovered after endotoxin instillation were similar to those identified in 11 patients with ARDS.[41](#_ENREF_41)

Accordingly, we are the first group to develop a noninvasive imaging approach that can quantify the anti-inflammatory effect of a drug in a human model of experimentally-induced lung inflammation[37](#_ENREF_37). We validated the application of FDG-PET imaging in a canine model of acute lung injury. We next used this imaging approach to quantify experimentally-induced lung inflammation in healthy volunteers in a model first characterized at the NIH[35](#_ENREF_35). Finally, we successfully used this human model of lung inflammation to demonstrate that lovastatin effectively suppresses the lung’s inflammatory response using FDG-PET as the primary outcome measure[37](#_ENREF_37). Therefore, *we are uniquely qualified to study the effect of novel anti-inflammatory treatments on the levels of neutrophil activation and recruitment as measured by FDG-PET*.

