## Outpatient Drug Treatment

Each volunteer receiving endotoxin will take the following:

- Pioglitazone 45 mg or matching placebo by mouth once daily for 2 weeks prior to admission.
- Zileuton 600 mg or matching placebo by mouth with food qid for 5 days prior to admission.

Volunteers enrolled to undergo BAL only will not be treated with any medications, including placebo.

- - 1. Justification for Dosing

There are no data indicating what dosing regimen for pioglitazone would be optimal for specifically reducing lung inflammation in humans. Several clinical trials in patients with diabetes have demonstrated decreases in human serum C-reactive protein levels with pioglitazone treatment (45 mg/day) for 8 weeks or longer. One study evaluated the ability of pioglitazone to reduce inflammatory markers and vascular changes in response to systemic endotoxin administration in healthy volunteers[68](#_ENREF_68). This particular study did not report any significant impact on TNF-alpha or IL-6 production in the blood at 2 or 4 hours after endotoxin in healthy volunteers who had been taking 60 mg of pioglitazone daily for 9 days. Since pioglitazone serum levels reach steady-state only after 7 days of drug administration, it is possible that the volunteers did not take the drug for a long enough period of time to have an anti-inflammatory effect. We also know that responses in the lungs to endotoxin may differ from that in the systemic circulation[69](#_ENREF_69), so while this study provides a benchmark for determining the dose for this study, the results may not be reflective of what would happen in the lungs after endotoxin exposure. Two studies have reported 9-day dosing in healthy volunteers at 45 and 60 mg per day without any serious side effects. Clinical trials of 8 and 12 weeks’ duration have been conducted in patients with diabetes with pioglitazone without serious side effects attributable to the drug. Based on the available information we have about pioglitazone, we have chosen to give volunteers 45 mg daily for 2 weeks for this particular study.

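### The interim rule measures pioglitazone's effect from the pre-endotoxin baseline, so a fully effective drug is expected to show no change and lose the combination group

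*Protocol*

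**What the plan says.** Section 6.2 (Statistical Analysis) and the Summary (Statistical Methods) carry the same rule, applied once the pioglitazone plus placebo group is filled. "If there is a minimum of a 30% drop in the post-endotoxin" Ki relative to the baseline Ki, "enrollment will continue into the next 3 groups". If no change in Ki is observed, the zileuton and placebo groups are still enrolled, "but will not enroll volunteers into the pioglitazone+zileuton group".

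The Summary (Trial Design) fixes what baseline means: volunteers "undergo a baseline FDG-PET scan on Admission Day 1, receive endotoxin on Admission Day 2, and undergo a post-endotoxin FDG-PET scan" on Day 3. Section 4.2 adds that the drug is already on board at that first scan: "Pioglitazone 45 mg or matching placebo by mouth once daily for 2 weeks prior to admission".

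Section 2.1 gives the purpose of the rule: to remove the combination group if the pioglitazone dose proves ineffective. Section 1.2 states hypotheses 1 and 2 as a lower Ki relative to placebo. Section 6.1 sizes the trial on a roughly 50% decrease in Ki "after treatment with lovastatin when compared to placebo". Placebo is the last of the four groups to be enrolled.

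**The concern.** The volunteers are healthy, and the inflammation under study does not exist until Day 2. The Background (section 1.1) reports of the same model: "Neutrophil concentrations in the BAL from challenged lung segments increased by 32-fold 24 h after endotoxin instillation". It also says that activated neutrophils take up the tracer. Ki should therefore rise between the two scans, and an anti-inflammatory drug works by limiting that rise. Two weeks of pioglitazone precede the baseline scan, so any effect on resting uptake is already in the baseline value.

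Complete success then means a post-endotoxin Ki equal to baseline, which is the result the rule reads as an ineffective dose. The rule also assigns no action to a rise, or to a fall of less than 30%, and these are the likely results for a partly effective or inert drug.

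At stake is whether the combination group is enrolled at all. Section 6.2 says that the hypotheses could still be adequately tested without it. Hypothesis 3 compares the combination with pioglitazone alone, so it could not be tested, and the factorial analysis would lose its fourth cell.

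**Working it through.** **Inputs from the Protocol.** Threshold 30% drop from baseline (6.2); n = 6 at the interim (3.4, 6.2); planning effect about 50% versus placebo, SD about 25%, residual SD 23%, power 0.8, alpha 0.05 (6.1).

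**Assumptions.** The size of the endotoxin-induced rise in Ki is not given. Call it r, as a fraction of baseline, and try 25% to 300%. The SD of within-person percent change is not given either. The 23% to 25% of section 6.1 is borrowed, with 35% and 50% as wider cases.

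**The plan's own figure.** A two-sided two-sample t-test with difference 50 and SD 25 has power 0.79 at n = 5 and 0.876 at n = 6 per group. N = 6 reproduces, on a comparison with placebo.

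**Expected change under the interim rule.** If the drug prevents a fraction f of the rise, the expected change from baseline is r × (1 − f). Reaching −30% needs f = 1 + 0.3/r.

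| Rise r | Inert (f = 0) | Half prevented (f = 0.5) | Fully prevented (f = 1) | f needed for −30% |
|---|---|---|---|---|
| 25% | +25% | +12.5% | 0% | 2.2 |
| 50% | +50% | +25% | 0% | 1.6 |
| 100% | +100% | +50% | 0% | 1.3 |
| 200% | +200% | +100% | 0% | 1.15 |
| 300% | +300% | +150% | 0% | 1.10 |

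The 0% for full prevention does not depend on r. A true 30% drop always needs more than 100% prevention.

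**Chance that a fully effective drug passes.** P(mean change ≤ −30) = Φ(−30 / (SD/√6)).

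- SD 23: Φ(−30/9.39) = 0.07%
- SD 25: Φ(−30/10.21) = 0.16%
- SD 35: Φ(−30/14.29) = 1.8%
- SD 50: Φ(−30/20.41) = 7.1%

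**Planning effect read as Ki 50% below placebo.** The change from an untreated baseline is 0.5 × (1 + r) − 1, which is −37.5%, −25%, 0%, +50% and +100% for the five values of r. It reaches −30% only if (1 + r) ≤ 1.4, that is, if endotoxin alone raises Ki by no more than 40%. Ki would then have to end below its resting level.

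**A placebo-referenced rule.** Compare mean absolute post-endotoxin Ki, 6 versus 6, with the SD as a percentage of placebo Ki. The standard error is SD × √(2/6), or 13.3 at SD 23 and 14.4 at SD 25.

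- True 50% reduction: Φ((50 − 30)/13.3) to Φ((50 − 30)/14.4), about 93% to 92% pass.
- Inert drug: Φ(−30/13.3) to Φ(−30/14.4), about 1.2% to 1.9% pass.

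**The same threshold on the endotoxin-induced change.** As a share of the placebo rise, the SD becomes SD × (1 + r)/r, ignoring baseline noise and correlation. An inert drug then passes about 7% to 8% of the time at r = 200%, 13% to 15% at r = 100%, and 23% to 24% at r = 50%. The two statistics are not interchangeable.

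**The case against.** A baseline reference is not foreign to this plan. The first primary endpoint is the change in Ki between the two scans, and hypothesis 3 compares the combination with pioglitazone alone. A reader might infer that every effect in the plan is measured against placebo, but that is not so. What stands is narrower: efficacy in hypotheses 1 and 2 and the planning effect in section 6.1 are relative to placebo, and no concurrent placebo data exist at the interim.

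A reader might also infer that an effective drug can never meet the rule. The document does not support that. Chance can produce a 30% mean drop, and a Ki halved relative to placebo passes when the rise is only 25%. The 32-fold figure describes neutrophils in lavage fluid, not Ki. The text therefore supports the direction of the Ki change but not its size. The SD is also borrowed from a drug-versus-placebo comparison. These points limit how firmly the result can be worded, but the expected 0% under full prevention depends on neither the size of the rise nor the SD.

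The sponsor may have meant a 30% reduction against a placebo or historical response. The text does not say so, and the same wording appears twice.

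**Conclusion.** The rule is wrong as written. Followed literally, it is expected to send a fully effective drug to the branch meant for an ineffective dose, with a pass chance of about 0.07% to 0.16% at the protocol's SDs and about 7% at an SD of 50%. It also gives no decision for a rise or for a fall short of 30%. This rests on endotoxin raising Ki, which the Background supports, and on the drug acting by limiting that rise.

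A reader might conclude that the whole trial is compromised. It is not. The pioglitazone, zileuton and placebo groups are enrolled under either stated branch, so the comparisons in hypotheses 1 and 2 are unaffected. The possible loss is hypothesis 3 and the fourth factorial cell. Because the rule governs enrolment, it needs correcting before the first group is filled.

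**What to change.** Enrol placebo before the decision and the combination group last. State one statistic and one threshold in both section 6.2 and the Summary: open the combination group if mean absolute post-endotoxin Ki on pioglitazone is at least 30% below concurrent placebo, and otherwise do not. Every outcome then has an action.

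Do not offer the endotoxin-induced change as an alternative statistic, because its error rates differ and depend on a rise that the document does not give. Do not substitute the placebo group of the earlier lovastatin study, because its values, size and comparability are not in the document.

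No extra volunteers are needed. The combination still follows both single-drug groups, which keeps the safety reason for sequential enrolment in sections 2.1 and 5.7. The cost is a later decision: after three groups (18 completers) instead of one (6).
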